## Abstract

**Background:**

Various priming techniques to enhance neuroplasticity have been examined in stroke rehabilitation research. Most priming techniques are costly and approved only for research. Here, we describe a priming technique that is cost-effective and has potential to significantly change clinical practice. Bilateral motor priming uses the Exsurgo priming device (Exsurgo Rehabilitation, Auckland, NZ) so that the less affected limb drives the more affected limb in bilateral symmetrical wrist flexion and extension. The aim of this study is to determine the effects of a 5-week protocol of bilateral motor priming in combination with task-specific training on motor impairment of the affected limb, bimanual motor function, and interhemispheric inhibition in moderate to severely impaired people with stroke.

**Methods:**

Seventy-six participants will be randomized to receive either 15, 2-h sessions, 3 times per week for 5 weeks (30 h of intervention) of bilateral motor priming and task-specific training (experimental group) or the same dose of control priming plus the task-specific training protocol. The experimental group performs bilateral symmetrical arm movements via the Exsurgo priming device which allows both wrists to move in rhythmic, symmetrical wrist flexion and extension for 15 min. The goal is one cycle (wrist flexion and wrist extension) per second. The control priming group receives transcutaneous electrical stimulation below sensory threshold for 15 min prior to the same 45 min of task-specific training. Outcome measures are collected at pre-intervention, post-intervention, and follow-up (8 weeks post-intervention). The primary outcome measure is the Fugl-Meyer Test of Upper Extremity Function. The secondary outcome is the Chedoke Arm and Hand Activity Index-Nine, an assessment of bimanual functional tasks.

**Discussion:**

To date, there are only 6 studies documenting the efficacy of priming using bilateral movements, 4 of which are pilot or feasibility studies. This is the first large-scale clinical trial of bilateral priming plus task-specific training. We have previously completed a feasibility intervention study of bilateral motor priming plus task-specific training and have considerable experience using this protocol.

**Trial registration:**

ClinicalTrials.gov NCT03517657. Retrospectively registered on May 7, 2018.

**Supplementary Information:**

The online version contains supplementary material available at 10.1186/s13063-022-06465-9.

## Administrative information

Note: the numbers in curly brackets in this protocol refer to SPIRIT checklist item numbers. The order of the items has been modified to group similar items (see http://www.equator-network.org/reporting-guidelines/spirit-2013-statement-defining-standard-protocol-items-for-clinical-trials/).

## Introduction

### Background and rationale {6a}

The decline in stroke mortality over the twentieth century [1] has increased incidence of post-stroke disability, and the most common disability in the stroke population is upper extremity (UE) hemiparesis. Constraint-induced movement therapy (CIMT) is an effective intervention but is only appropriate for stroke survivors with mild UE impairment who are in the upper quartile of residual function [2]. Thus, alternative treatments are needed to target stroke survivors with more moderate and severe impairments of the UE, whose prognosis for motor recovery is less favorable.

In an observational study, Ward and colleagues [3] demonstrated a large improvement in the Fugl-Meyer Test of Upper Extremity Function (FMUE) median score (FMUEΔ 8.0, IQR=4–11) in severely impaired individuals after 90 h of various types of occupational therapy. While the improvement was impressive, the study did not inform about the superiority of any specific training. Also, 90 h of training is a very large dose that is not sustainable in the current healthcare climate in the USA. Other studies using unilateral training for individuals with severe UE impairment have shown improvements that can be described as modest at best including robotic training (FMUEΔ = 1.11 ± 1.01) [4]; unilateral task-specific training in an active comparator group (FMUEΔ = 3.1 ± 5.3) [5]; and task-specific training + robotics (FMUEΔ = +3.25 ± 1.68) [6]. These studies did not demonstrate an improvement in the FMUE of ≥ 4.25 which is the estimated clinically important difference [7]. More impaired individuals may need either a larger dose or an augmentative intervention.

Motor priming is a construct used to describe a variety of techniques that optimize the brain’s response to subsequent training and may enhance neuroplasticity and motor performance [8–10]. Shiner et al. [11] compared bilateral motor priming (BMP) plus Wii therapy to Wii therapy alone in subacute and chronic stroke subjects. The result was in favor of the bilateral priming plus Wii training group that, at follow-up, had a significantly greater mean FMUE [12] score than with Wii training alone (6.3 between-group difference) [11]. There was a large range of impairment levels in the Shiner et al. study, and those individuals with more severe impairment had the largest improvement. This result suggests that BMP may magnify improvements inherent in therapy protocols and facilitate sustained improvements over time in individuals with severe UE impairment. Stoykov and colleagues [13] used a task-specific training (TST) protocol and combined it with either BMP or stroke education (control). The bilateral priming group had a substantial increase in FMUE scores from pre-intervention to follow-up (FMUEΔ = 10 ± 6.1) while the improvement in the control group was modest (FMUEΔ = 3.56 ± 4.1.) These data were used as the pilot data for the grant submission.

Another priming + TST study examining UE hemiparesis in severely impaired participants used sensory-based priming plus TST [14] compared to TST alone, and the between-group differential of the FMUE was highest at follow-up (between-group FMUEΔ was 4.4 ± 1.1). This finding is consistent with other studies confirming that the largest difference between priming and control group is at follow-up [13–18].

This clinical trial examines the use of BMP, a non-invasive, cost-effective neuromodulation technique. BMP consists of continuous, bilateral wrist flexion and extension using a device with a mechanical linkage so that the less affected hand and the more affected one move in symmetry [19]. This study is a pivotal step towards developing and using a practical neuromodulatory technique to prime the central nervous system to respond with greater efficacy to behavioral interventions for people with moderate to severe UE hemiparesis. In addition to the benefits mentioned above and compared to priming using more invasive methods such as repetitive transcranial magnetic stimulation (rTMS), BMP is (1) cost-effective; (2) available to a larger pool of people due to the absence of safety concerns; (3) does not require a skilled operator; and (4) can potentially be implemented into the clinic [20]. There are no known risks to bilateral priming.

### Objectives {7}

The purpose of this study is to test the hypothesis that bilateral symmetrical arm movements prime cortical regions and enhance neuroplasticity as measured by behavioral and cortical measures. Specifically, this trial will address two main objectives and test their associated hypotheses. The primary objective is to determine the magnitude of change in upper limb function and impairment in chronic stroke survivors who have undergone 30 h of BMP + TST. Primary hypothesis 1.1 is that the combination of BMP + TST will produce a between-group difference in improvement on the FMUE of at least 6.0 points more than control priming (CP) + TST at the follow-up timepoint (8 weeks post-treatment cessation). Secondary hypothesis 1.2 is that the combination of BMP + TST will increase scores on the Chedoke Arm & Hand Activity Index (CAHAI-9) by 3 points more than CP + TST, 8 weeks after the post-test (follow-up).

The secondary objective is to determine the effects of bilateral priming on cortical mechanisms measured by TMS. Hypothesis 2.1 is that BMP + TST will increase TCI from ipsilesional to contralesional hemisphere at post-treatment (following 30 h of treatment) and at 8 weeks after treatment cessation (follow-up), but there will be no change in the CP + TST group. Hypothesis 2.2 is that an increase in ipsilesional TCI will be positively associated with changes in the FMUE. We will perform a correlation analysis to test this relationship.

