### Sample size {14}

We are enrolling 38 subjects per group (*N* = 76). Allowing for the attrition of 12 participants (15% based on our pilot study [13]), we project at least 32 subjects per group will have both the baseline and follow-up data required to compute our change outcomes at 8 weeks post-treatment cessation. For the hypotheses tested for objectives 1 and 2, we will evaluate between-group (BMP+TST vs. CP+TST) differences using analyses of covariance (ANCOVA) that adjust for the outcome measure at baseline; tests will be two-sided at the 5% level (*α* = 0.05). The power of these tests depends on the number of participants in each group, the separation of the means of each group, the significance level, the population standard deviation (SD) of the outcome measures, and the correlation between measures at baseline and follow-up. We consider what sample size per group (*n*) will provide 90% or greater power.

We discuss each of the two objectives in turn. Table 2 presents the primary outcome measure (FMUE), secondary outcome measure (CAHAI-9), and the additional outcome measure (TCI in objective 2). For each measure, the table shows the difference in the group means that can be detected with 90% power assuming *N*=32 per group, along with the hypothesized SD of the outcome. Power computations assume a modest correlation between baseline and follow-up for measures of *R*^2^ = 0.2. To derive our estimates of the SD of outcome measures at follow-up (8 weeks post-treatment cessation), we used the results of a published pilot study at 6 weeks post-treatment cessation [13].

**Table 2 Tab2:** Sample size analysis: primary and secondary measures

	Mean difference	SD

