**Aim 2**		
**TCI**	2.74	3.71

Effects detectable with 90% power for Aims 1 and 2

*Abbreviations*: *SD* standard deviation of the change score (follow-up–pre), *FMUE* Fugl-Meyer Upper Extremity Function, *CAHAI-9* Chedoke Arm & Hand Activity Index-Nine, *TCI* transcallosal inhibition

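### The 90% power aim covers the hypotheses of both objectives, but Table 2 meets it for CAHAI-9 only at 5.34 points, not the hypothesised 3, where power is about 44%

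*Protocol article*

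**What the plan says.** - **Objectives {7}.** Hypothesis 1.1 (primary) expects an FMUE advantage of at least 6.0 points at the 8-week follow-up. Hypothesis 1.2 (secondary) expects that the experimental treatment "will increase scores on the Chedoke Arm & Hand Activity Index (CAHAI-9) by 3 points more than CP + TST" at the same time point. Both belong to the primary objective.
- **Sample size {14}, scope.** The analysis and power paragraph opens with "For the hypotheses tested for objectives 1 and 2, we will evaluate between-group" differences by ANCOVA adjusted for baseline, and "tests will be two-sided at the 5% level". It then asks what number per group "will provide 90% or greater power".
- **Sample size {14}, numbers.** "We are enrolling 38 subjects per group"; after attrition of 12 participants, "we project at least 32 subjects per group will have both the baseline and follow-up data". The assumed relation between baseline and follow-up is R² = 0.2.
- **Table 2.** According to the text, "the table shows the difference in the group means that can be detected with 90% power" with 32 per group. The rows are FMUE 5.98 (SD 8.11), CAHAI-9 5.34 (SD 7.26) and TCI 2.74 (SD 3.71). The footnote defines SD as "standard deviation of the change score (follow-up–pre").
- **Hypothesis 1a and 1b analysis.** FMUE and CAHAI-9 are both placed under the primary confirmatory analyses, each with a two-sided 5% test.

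**The concern.** For FMUE the two sections agree: 6.0 points hypothesised, 5.98 detectable. For CAHAI-9 they do not: 3 points hypothesised, 5.34 detectable, a ratio of 5.34 / 3 = 1.78. The article neither mentions the gap nor gives power for 3 points. TCI has no numerical hypothesis, so CAHAI-9 is the only row of Table 2 that fails to cover an effect stated elsewhere in the article.

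What is at stake is how a null result would be read. CAHAI-9 is the only outcome named as secondary, and it gets a confirmatory 5% test. A reader who takes the 90% aim to extend to hypothesis 1.2 would treat a non-significant CAHAI-9 result as good evidence against a 3-point benefit. On the planning inputs, a true 3-point benefit would be missed somewhat more often than it was found.

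**Working it through.** **Inputs**, all from Sample size {14} and Table 2 except the hypothesised differences, which are in Objectives {7}: SD 7.26 for CAHAI-9; R² = 0.2; 32 analysed per group (38 enrolled); two-sided α = 0.05; hypothesised difference 3 points.

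**Formulas.** Residual SD = SD × √(1 − R²). Standard error of the group difference = residual SD × √(2/n). Noncentrality = difference / standard error. Power comes from the noncentral t distribution with 2n − 3 degrees of freedom (two group means and one covariate).

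**Step 1: reproduce Table 2** (n = 32, so √(2/32) = 0.25 and df = 61).

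| Outcome | Residual SD | SE | Stated difference | Noncentrality | Power |
|---|---|---|---|---|---|
| FMUE | 8.11 × √0.8 = 7.25 | 1.81 | 5.98 | 3.30 | 90.1% |
| CAHAI-9 | 7.26 × √0.8 = 6.49 | 1.62 | 5.34 | 3.29 | 89.9% |
| TCI | 3.71 × √0.8 = 3.32 | 0.83 | 2.74 | 3.30 | 90.2% |

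Solving for exactly 90% gives 5.97, 5.35 and 2.73. All three rows reproduce, so this is in effect the plan's own method.

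**Step 2: the same method at the hypothesised CAHAI-9 difference.** Noncentrality = 3 / 1.62 = 1.85; critical t (61 df) = 2.00; power = 44.4%. The normal approximation gives 45.5%.

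**Step 3: variations on the stated inputs.**

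| Case, difference of 3 points, SD 7.26 | Power |
|---|---|
| 32 per group, R² = 0.2 (as planned) | 44.4% |
| 38 per group, R² = 0.2 (no attrition) | 51.1% |
| 32 per group, 0.2 read as a correlation, not R² | 38.2% |
| 32 per group, no gain from the covariate | 37.0% |

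**Step 4: distance from 90%.** Changing one input at a time, 90% power for 3 points would need about 100 analysed per group (90.2%), or R² of about 0.75 (90.2%), or an SD of about 4.07 (90.0%).

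**Step 5: expected precision.** With 32 per group the 95% confidence interval has an expected half-width of 2.00 × 1.62 = 3.2 points. An observed difference of exactly 3 points would therefore typically not be significant.

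**The case against.** **Table 2 claims nothing false.** It is a table of detectable differences, it prints 5.34 openly, and a reader can see that 3 is smaller. This stands. One might infer that the protocol asserts 90% power for 3 points, or that Table 2 is miscalculated. The documents support neither: no sentence attaches 90% power to 3 points, and every row of the table reproduces. What remains is that the section frames its 90% aim for the hypotheses of both objectives, including 1.2, and then presents a figure that does not meet the aim for that hypothesis without saying so.

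**Secondary outcomes need not be powered.** This also stands. The trial is sized coherently on its primary hypothesis. It would be wrong to infer that the trial is undersized overall or should be enlarged. But this article chose to give CAHAI-9 a numerical hypothesis, a 90% power row and a confirmatory test, so the figures should be reconciled.

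**The 44% depends on uncertain inputs.** It does. The text describes the SDs as those of outcomes at follow-up, while the table footnote calls them SDs of change. The FMUE SD of 8.11 exceeds the pilot change SDs in Background and rationale {6a} (6.1 and 4.1; pooled √((6.1² + 4.1²)/2) = 5.2, assuming equal groups). The pilot CAHAI-9 SD is not given. If, purely as an assumption, 7.26 were too large by the same ratio (8.11 / 5.2 = 1.56), the SD would be about 4.65 and power for 3 points about 81%, or 72% without covariate gain. With SD 7.26 and R² = 0.5 it would be about 63%. So the statement that a 3-point benefit is missed more often than found holds only on the planning inputs. None of these scenarios reaches 90%.

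**The reporting is partly in place.** The analysis section already promises point estimates and standard errors, from which an interval follows. That reduces the change needed but does not correct the power statement.

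**Conclusion.** The inconsistency is real and should be fixed, but it is not a critical fault. The sample size section aims at 90% power or more for hypotheses that include a 3-point CAHAI-9 difference; its own table gives 90% only at 5.34 points. Given SD 7.26, R² = 0.2 and a two-sided 5% test, power for 3 points is about 44% with 32 analysed per group and about 51% with all 38. These figures are conditional on that SD and R² and would rise if the true SD were smaller or the baseline correlation stronger. Power for the primary FMUE hypothesis is unaffected.

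**What to change.** Add a short statement beside Table 2 in Sample size {14}, for example:

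*The aim of 90% power holds for the FMUE hypothesis. For CAHAI-9 it holds only for a difference of 5.34 points; under the same assumptions (SD 7.26, R² = 0.2, 32 per group, two-sided 5%), power for the hypothesised 3 points is about 44%. CAHAI-9 will be interpreted by its estimated difference and 95% confidence interval, and a non-significant result will not be read as refuting a 3-point benefit.*

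Hypothesis 1.2 itself can stay as worded. The cost is wording only, with a less favourable stated power for the secondary outcome. Sample size, data collection and the analysis models do not change. The article says that analysis will follow once all participants have completed, so the statement can be made before results are known.

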### Trial design {8}

This protocol adheres to the guidance of the Standard Protocol Items: Recommendations for Interventional Trials (SPIRIT) statement for reporting randomized clinical trials [21]. The study design is a stratified, randomized, masked, and parallel, two-arm intervention study of the effects of BMP and TST. This is a two-site superiority trial.

## Methods: participants, interventions, and outcomes

### Study setting {9}

Assessments are performed at the Northwestern University Department of Physical Therapy and Human Movement Science (PTHMS). Prior to the COVID-19 pandemic, treatment intervention and some of the assessments occurred at the Shirley Ryan AbilityLab. Northwestern University human subjects’ research was closed in March of 2020. Research resumed in July of 2020 but with significant restrictions specifying number of participants per research lab and strict adherence to protective equipment for both investigators and participants. Due to these restrictions, and preferences of the study team, the investigators decided to use both the Northwestern PTHMS Department and Shirley Ryan AbilityLab for treatment. Assessments are now only performed at Northwestern PTHMS Department. Both locations are in Chicago, Illinois.

### Eligibility criteria {10}

Inclusion and exclusion criteria can be found in Table 1.

**Table 1 Tab1:** Inclusion and exclusion criteria

Inclusion criteria	Exclusion criteria
(a) Evidence of a stroke without involvement of the cerebellum at least 6 months prior to enrollment	(a) Orthopedic conditions of either the less affected or affected wrist
(b) FMUE score between 23 and 38	(b) An MMSE score lower than 21
(c) 0 through 3 in wrist flexion and wrist extension on the Modified Ashworth Scale	(c) *A stroke in the cerebellum*
(d) Individuals who are at least 18 years old and have the ability to consent.	(d) *History of epilepsy, seizures, or convulsions*
	(e) Ringing in ears
	(f) Presence of cochlear implant
	(g) Presence of pacemaker or neurostimulator
	(h) History of persistent headaches
	(i) Metal implant or fragments of metal in head or neck area
	(j) Presence of other neurological conditions including PD or CP
	(k) History of head trauma or concussion with loss of consciousness
	(l) Received Botox in the affected UE within the past 6 months
	(m) Metastatic cancer
	(n) Prisoners, children, or pregnant women
	(o) Individuals under the age of 18
	(p) Any adult unable to consent

Eligibility criteria for clinicians working as standardized treatment therapists for this trial include being a registered and licensed occupational therapist. Assessments are performed by licensed occupational therapists who are not treating the participants. Research staff trained in TMS, collect the TMS data. A TMS safety checklist is administered to ensure no contraindications to TMS.

### Who will take informed consent? {26a}

If a participant is found to be eligible and wants to be in the study, informed consent is obtained by a research team member during the in-person screen. A model consent form is attached as an Additional file (see Additional file 2). The research is conducted in compliance with state and federal laws, including the Health Insurance Portability and Accountability Act (HIPAA) which requires researchers to protect and maintain confidentiality of an individual’s health information. All subjects are asked to sign an “Authorization to Use and Disclose (Release) Health Information for a Research Study.” All research staff are trained in proper procedures for obtaining informed consent.

Study staff complete all initial phone screens, in-person screens, and consenting of participants. “SOP: Informed Consent Process for Research (HRP-090)” is followed while obtaining consent from each individual participant.

### Additional consent provisions for collection and use of participant data and biological specimens {26b}

If the participant agrees, we collect videos of the participant performing functional tasks pre- and post-intervention. Videos are used to train therapists in the study protocol as well as demonstrate functional improvement during academic and scholarly presentations. The choice to videotape is clearly stated on the consent form. The participant has the right not to be videotaped. This trial does not involve collecting biological specimens for storage.

## Interventions

### Explanation for the choice of comparators {6b}

We are using the same treatment protocol as our pilot study. However, we have changed the comparator group design. The intervention for the control group (CP) is subthreshold electrical stimulation. We apply transcutaneous electrical nerve stimulation (TENS) to the volar aspect of the paretic arm for 15 min. The current is an asymmetrical biphasic square impulse waveform with a frequency of 40 Hz and a pulse width of 250 μs. The intensity is initially adjusted so that the subjects perceive the stimulation. It is then reduced to 1 milliamp (sub-sensory threshold) and maintained for 15 min*.* Consistent with our pilot study, we expect improvement in both groups. However, we expect a larger magnitude of improvement in the BMP group that will be most evident at follow-up.

Both groups participate in a different priming intervention but the same TST protocol. The difference between the comparators is the priming intervention. The choice of the subthreshold e-stim control group was to control for participant’s expectations and attention such that any difference between the two groups is due to BMP.

### Intervention description {11a}

There are fifteen, 2-h sessions of treatment over 5 weeks (approximately three times per week) for a total of 30 h of BMP + TST in the experimental group. The control group receives the same duration and schedule (30 h of CP + TST) for treatment. A sixth week is reserved for any make-up sessions needed. There are two, 1-h treatment sessions per study visit. A minimum 30-min break separates each hour of training. During the first session, participants receive 15 min of priming (either BMP or CP) followed by 45 min of therapist-selected activities from the TST protocol. The second hour includes 15 min of priming plus 45 min of training on tasks selected from the Canadian Occupational Therapy Measure (COPM) [22].

